### Trial design

The PT trial is designed as a randomized, controlled, experimental, open, single center, equivalence trial, with three-arm parallel groups. Randomization will be performed as block randomization with a 1:1 allocation.

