### Objectives

The objectives of this randomized clinical trial are: Investigate whether a behavioral parent training program, adapted from the model proposed by Alan Kazdin [22], is effective as a complementary treatment for ADHD and ODD, reducing externalizing symptoms; Investigate the effects of two modalities of parent training (online and face-to-face) on 1) externalizing symptoms reduction, 2) on childrens’ and parents’ quality of life, 3) on parenting style and 4) on stress perceived by the main caregiver, by comparing results before and after the intervention, in each of the modalities and between the modalities, checking out if the effects are similar; Evaluate the effects of parent training in both modalities (online and face-to-face) in short term; Evaluate if there is a moderating effect of the parents’ intelligence, schooling, socioeconomic level, and symptoms of depression, anxiety and ADHD, on intervention response, in each of the parent training modalities (online and face-to-face); Evaluate if there is a moderating effect of the child’s age and school performance on intervention response, in each of the parent training modalities (online and face-to-face).

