### Interventions

#### Interventions

Participants will be randomly assigned to either control or one of the experimental groups with a 1:1 allocation as per a computer-generated randomization schedule stratified by children’s age using five permuted blocks of 6 participants.

**GROUP 01:** 30 participants. Conventional treatment, without complementary treatment. Bi-monthly consultations with a child and adolescent psychiatrist, including drug treatment if there is a clinical indication (at medical discretion, according to the clinical protocol), and without any other type of complementary treatment.

**GROUP 02:** 30 participants. Conventional treatment and behavioral intervention in face-to-face format. Bi-monthly consultations with a child and adolescent psychiatrist, including drug treatment if there is a clinical indication (at medical discretion, according to the clinical protocol), and complementary behavioral intervention: parent management training, in face-to-face format, with a specialized therapist, in six sessions held on a weekly basis, adapted from the “Parent Management Training” manual developed by Alan Kazdin [22].

**GROUP 03:** 30 participants. Conventional treatment and behavioral intervention in online format. Bi-monthly consultations with a child and adolescent psychiatrist, including drug treatment if there is a clinical indication (at medical discretion, according to the clinical protocol), and complementary behavioral intervention: parent management training, in online format, on a platform developed for the study, in six modules, to be carried out on a weekly basis, adapted from the “Parent Management Training” manual developed by Alan Kazdin [22].

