### Sample size

A sample of 90 participants would be sufficient to detect a small (d = 0.2) to high (0.8) association with a small (0.4) covariance between repeated measures (intraclass correlation coefficient—ICC = 0.9) and an association of moderate (0.5) to high for larger ICCs (0.6 to 0.9).

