### Statistical methods

#### Outcomes

The main analysis strategies will involve techniques for group comparison (ANOVA etc.), analysis of repeated measures (mixed models, GHG etc.), as well as correlation and regression to verify the association between variables. Techniques will be chosen depending on data distribution. If necessary, depending on the sampling power, we will employ techniques resampling.

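### The trial is labelled an equivalence trial, but no margin or equivalence comparison is stated, the sample size and named tests are aimed at differences, and 30 per arm is not shown to be adequate for equivalence

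*Protocol article*

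**What the plan says.** Under Trial design the article says: "The PT trial is designed as a randomized, controlled, experimental, open, single center, equivalence trial, with three-arm parallel groups". The Objectives section sets out a pre-post comparison of outcomes, to be made "in each of the modalities and between the modalities, checking out if the effects are similar". That is the only place where a criterion for the comparison of formats is suggested, and it carries no figure.

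The Sample size section says "A sample of 90 participants would be sufficient to detect a small (d = 0.2) to high (0.8) association". For this first scenario the stated condition is "with a small (0.4) covariance between repeated measures" (an ICC of 0.9 stands in the same phrase). For a second scenario it gives "an association of moderate (0.5) to high for larger ICCs (0.6 to 0.9". Alpha, power and the test are not given there. The Interventions section puts 30 participants in each of the three groups.

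The Outcomes paragraph under Statistical methods begins "The main analysis strategies will involve techniques for group comparison (ANOVA etc" and goes on to mixed models, correlation and regression. The Additional analyses paragraph names ANOVA post hoc tests.

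The first objective and the Choice of comparators section also ask whether parent training adds benefit to conventional treatment.

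**The concern.** An equivalence design reverses the usual logic. The hypothesis to be rejected is that the two treatments differ by at least a stated margin, and that margin determines the sample size. Here the declared design has no margin, while the sample-size sentence and the named tests address the opposite question, whether a difference can be detected.

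Failing to find a difference does not show that there is none. With no other criterion for similar effects in the article, a non-significant post hoc test between online and face-to-face training could be taken as the answer. The Introduction and Discussion present online delivery as a cheaper, wider-reaching alternative to therapist-led sessions, so a mistaken finding of similarity would have practical consequences.

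The single label also does not fit the rest of the trial. Each training format against standard care is a superiority question.

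**Working it through.** **1. Passages set side by side.** Trial design: equivalence. Objectives: similar effects between formats, plus effectiveness as an add-on. Sample size: effects to detect. Statistical methods: group comparison, repeated measures, post hoc tests. No section links the first to the last through a margin, and none names the equivalence comparison.

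**2. The plan's own figure.** N = 90 cannot be reproduced as a whole, because alpha, power and test are missing. Assume two-sided alpha 0.05, 80% power, and the 0.4 read as the pre-post correlation r.

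- Change score, d = 0.8, r = 0.4: n per arm = 2 × 2(1 − 0.4) × (1.96 + 0.842)² / 0.8² = 29.4, so 30 per arm and 90 in total. This one case matches.
- d = 0.2, pairwise, 30 per arm: power is about 11% (change score) or 13% (ANCOVA) at r = 0.4, and about 41% or 43% at r = 0.9.
- The overall group-by-time F test with d = 0.2 (f = d/2 = 0.1) and r = 0.9 has about 97% power at N = 90. It does not isolate online against face-to-face.

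Every calculation that fits the sentence is one for a difference. None uses a margin.

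**3. What 30 per arm gives for equivalence.** Inputs from the article: 30 per arm, two measurements, and values of 0.4, 0.6 and 0.9 from the Sample size section. Assumptions: ICC read as pre-post correlation r, ANCOVA, normal approximation, two one-sided tests at 5% each, true difference 0.

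- SE in SD units = √[(1 − r²) × 2/30]
- Smallest margin with 80% power = (1.645 + 1.282) × SE
- Power at margin m = 2Φ(m/SE − 1.645) − 1, set to 0 when negative

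| r | SE | Smallest margin, 80% power | Power at 0.30 SD | at 0.40 SD | at 0.50 SD |
|---|---|---|---|---|---|
| 0.4 | 0.237 | 0.69 | 0% | 4% | 36% |
| 0.6 | 0.207 | 0.60 | 0% | 23% | 56% |
| 0.9 | 0.113 | 0.33 | 69% | 94% | 99.5% |

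The margins in the last three columns are illustrations, since the article fixes none. With change scores, where the SD factor is √[2(1 − r)], the smallest margins become 0.83, 0.68 and 0.34 SD.

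**4. How often a real difference gives p > 0.05.** Take a true online deficit of 0.4 SD and a two-sided 5% test. The probability of non-significance is approximately Φ(1.96 − 0.4/SE).

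- r = 0.4: 0.4/0.2366 = 1.69, giving 61%
- r = 0.6: 0.4/0.2066 = 1.94, giving 51%
- r = 0.9: 0.4/0.1125 = 3.55, giving 5.5%

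**5. Exclusions.** The Analysis population and missing data section removes participants who do not complete the intervention or the outcome data, and the Sample size section states no allowance for loss. If 24 per arm were analysed (an illustrative 20% loss), the smallest margins rise to 0.77, 0.68 and 0.37 SD.

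**The case against.** The strongest defence is that a condensed article may leave the exact test procedure and CI level to a full protocol or analysis plan. The list of methods is also open-ended, and a mixed model or regression gives an estimate and interval that can be set against a margin. This stands as far as it goes: the absence of a named two one-sided tests procedure is not the fault. It does not cover the contradiction, because the article does give a sample-size rationale, and that rationale belongs to a different kind of design.

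Three stronger readings are tempting, and the article does not support them.

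- A reader might infer that 30 per arm cannot show equivalence. That depends on a margin and a correlation that are not fixed. At r = 0.9, inside the article's own ICC range, power is 94% for a margin of 0.40 SD and 69% for 0.30 SD.
- A reader might infer that the plan will report non-significance as similarity. No section says so. It is only a risk left open because no other criterion is given.
- A reader might take d = 0.61 from the Introduction as the expected effect and scale a margin from it. That figure averages digital programmes in studies that reported positive outcomes. It is not this trial's planned effect, and it does not compare face-to-face training with standard care.

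It is also fair to say that similarity of formats is not the only aim. The Choice of comparators section holds that online training may be of benefit whatever its standing against the traditional format. That weakens the equivalence label further.

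**Conclusion.** The point holds as an internal contradiction: equivalence is declared, but no margin or comparison is named, the sample size is framed as detection of effects, and the named group comparisons test for differences. The superiority questions against standard care fall outside the label altogether.

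On size, 30 per arm has not been shown to be adequate. It may be adequate if the correlation is near 0.9 and a margin of roughly a third of an SD or wider can be justified. At 0.6 or below it would take a margin of about 0.6 SD or more. The probability of missing a 0.4 SD deficit ranges just as widely, from about one in eighteen to about three in five. These figures rest on the assumed alpha, power, zero true difference, ANCOVA and the reading of ICC as pre-post correlation, and they precede any exclusions.

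**What to change.** Under Trial design, drop the equivalence label and describe each training format against standard care as a superiority comparison. Under Objectives and Statistical methods, say that online minus face-to-face will be reported as an estimate with a 95% CI, and that a non-significant difference will not be reported as similar or equivalent.

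If the sponsor prefers to keep equivalence:

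- name online versus face-to-face as the comparison to which it applies;
- state and justify a margin in advance;
- claim equivalence only if the 90% CI lies wholly inside that margin;
- restate under Sample size the power that 90 participants give for that margin across the assumed correlations, allowing for the planned exclusions.

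The first option costs only wording, and the claim about the two formats becomes more modest. The second needs a defensible margin and may show that 90 participants are too few, depending on the margin and correlation chosen.

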## Methods: Participants, interventions, outcomes

### Study setting

All groups will be invited to the Research Center of Impulsivity and Attention (NITIDA) at Hospital das Clínicas, UFMG–Brazil.

### Eligibility criteria

Participants inclusion criteria: Families whose children have Attention Deficit/Hyperactivity Disorder and/or Oppositional Defiant Disorder; children must have externalizing symptoms such as hyperactivity and/or oppositional behavior; children who are between 6 and 12 years old; male gender. Primary caregiver with complete high school education.

Participants exclusion criteria: Families whose children have severe psychiatric comorbidities (i.e. psychosis, bipolar affective disorder, severe depression), genetic or neurological; whose intelligence is below the 5th percentile; feminine gender. Families whose primary caregivers have intelligence below the 5th percentile or have been diagnosed with serious psychiatric conditions (i.e. psychoses, bipolar affective disorder, severe depression); and families with severe social adversity in the home context (i.e. domestic violence, physical abuse, extreme poverty, hunger). Primary caregiver without complete high school education.

All parents must sign the free and informed consent form, as well as the children the assent form. The terms will be delivered during the first consultation of the participants in the outpatient clinic, if they wish to participate voluntarily in the research. If there is more than one primary caregiver, it is recommended that everyone participate in the intervention. The effective participation of caregivers will be reported and analyzed along with the results.

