#### Modifications

The participant will be excluded from the survey if he does not attend or does not watch regularly the weekly sessions of the intervention. If the patient reports the impossibility of attending the session and is available to reschedule it within a maximum of 30 days, or in the case of the online group, watch the content up to a maximum of 30 days after the scheduled date, the patient can proceed with the intervention. The intervention does not offer any type of risk to the patient, and therefore discontinuity is only related to attendance.

Participants whose diagnosis on screening differs from the diagnosis of the psychiatry team will be excluded from the study.

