#### Adherence

The use of the platform is monitored, and the authors are notified at each stage completed by the participant. One day before the appropriate date for the execution of each module (a week apart between them) the platform automatically sends an e-mail, with the intention of reminding the participant of the commitment to the intervention and already anticipating a little of what will be seen in the next module (teaser). In addition, telephone contacts, when made available by the participant, enable direct contact if a delay in the deadlines is identified. Likewise, in the case of face-to-face meetings, the patient will be contacted frequently.

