#### Implementation

All patients who give consent for participation and who fulfil the inclusion criteria will be randomized. Randomization will be requested by the staff member responsible for recruitment and clinical interviews and will be performed by the computer technician, both members of NITIDA. In return, the computer technician will send an answer form to the study therapist who is not involved in assessing the outcome of the study. This form will include a randomization number. Closed envelopes with printed randomization numbers on it will be available for the therapist. For every randomization number the corresponding code for the therapy group of the randomization list will be found inside the envelopes. The therapist will open the envelope and will find the treatment condition to be conducted in this patient. The therapist then gives the information about treatment allocation to the patient. Staff responsible for recruitment and symptom ratings is not allowed to receive information about the group allocation.

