## Discussion

In Brazil, 74.9% of households have internet access, and 97% of these users use cell phones or tablets as a means of access, in addition to desktops or laptops [53]. Digital interventions are a strategy to overcome the barriers of the face-to-face modality, in addition to saving time and expenses by reducing the time spent with travel, planning, with the professional’s time and with the implementation of the in-person intervention [30]. Kazdin highlights the positive potential of these new forms of treatment, especially considering their reach to underserved families [54].

The use of technology and digital delivery is a growing parental training method, with high potential for reaching and sustainability, maximizing training fidelity, and engagement [30]. Engaging means engaging, and for this to really happen, the user needs to find, in addition to an attractive tool, a satisfying experience and fluid navigation, with design being an intersection point between technology and the transmission of knowledge, orchestrating and organizing resources to make this platform functional [55].

An online parent training platform was developed, which is a new (in the Brazilian context) and more accessible intervention technology aimed at low/medium income families with children who have externalizing problems. Low socioeconomic status is strongly related to negative outcomes in children with ADHD, such as poor school performance [28] and higher frequency of ODD as a comorbidity [29].

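### Eligibility does not check that a family can use the online platform, so a family without usable internet is excluded if allocated to Group 3 but can stay in Group 1 or 2

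*Protocol article*

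**What the plan says.** All references are to the protocol article.

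- **Eligibility criteria.** The inclusion list covers ADHD and/or ODD, externalizing symptoms, and "children who are between 6 and 12 years old; male gender. Primary caregiver with complete high school education". The exclusions include "families with severe social adversity in the home context (i.e. domestic violence, physical abuse, extreme poverty, hunger". Neither list mentions internet access or a device.
- **Implementation.** "All patients who give consent for participation and who fulfil the inclusion criteria will be randomized". No further check stands between eligibility and allocation.
- **Interventions.** Group 3 is "30 participants. Conventional treatment and behavioral intervention in online format", given as "parent management training, in online format, on a platform developed for the study, in six modules". The modules are videos of about 30 minutes each, followed by a quiz that must be passed. There is no therapist contact, and no offline route to the content is described.
- **Adherence.** "the platform automatically sends an e-mail, with the intention of reminding the participant of the commitment to the intervention".
- **Modifications.** "The participant will be excluded from the survey if he does not attend or does not watch regularly the weekly sessions of the intervention". A delay of up to 30 days is allowed.
- **Analysis population and missing data.** Families who do not complete the intervention or the outcome information are excluded from the study.
- **Retention.** If parents leave the training, post-intervention measures are still to be collected.
- **Discussion.** "In Brazil, 74.9% of households have internet access". The platform is aimed at families of low or medium income.

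**The concern.** Randomisation makes the three groups comparable only if families stay in the comparison whichever group they draw. Here, what happens to a family without internet depends on the draw. In Group 3 it cannot start the modules and falls under the exclusion rule. In Group 2 it can attend the sessions, and in Group 1 there is nothing to attend. Internet access is fixed before allocation and can be established by one question at screening.

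The protocol itself gives reason to think that the families lost would differ in prognosis. Its Introduction treats socioeconomic level as a moderator of ADHD symptoms and links low status to worse outcomes and more frequent ODD. The Objectives plan to examine socioeconomic level and schooling as moderators within each training format, and access-related loss would narrow that range in the online format alone. Randomisation is stratified by the child's age only. The planned look at socioeconomic data for sampling bias (Interim analyses) may reveal such a loss but cannot prevent it.

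**Working it through.** **Plan's own figure.** Three groups of 30 give 3 × 30 = 90, which agrees with the Sample size section. That section gives no significance level, power or test, so its power statement cannot be recomputed. This point does not depend on it.

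**Step 1: what happens to one family without usable internet.**

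| Allocation | Can it receive the allocated care? | Result under Modifications and the analysis-population rule |
|---|---|---|
| Group 1, usual care | Yes | Kept if outcomes are provided |
| Group 2, face-to-face | Yes, as far as internet is concerned | Kept if it attends and provides outcomes |
| Group 3, online | No | Excluded for not watching or not completing |

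Loss caused by lack of internet has expectation zero in Groups 1 and 2.

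**Step 2: how many families.** Let p be the proportion of eligible families without usable access. The expected number in Group 3 is 30 × p, and the chance of at least one is 1 − (1 − p)^30. Only the last row uses a figure from the document (1 − 0.749 = 0.251). The others are assumptions.

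| p | Expected of 30 | Chance of at least one |
|---|---|---|
| 0.05 | 1.5 | 1 − 0.95^30 = 0.79 |
| 0.10 | 3.0 | 1 − 0.90^30 = 0.96 |
| 0.15 | 4.5 | 1 − 0.85^30 = 0.99 |
| 0.251 | 7.5 | 1 − 0.749^30 = 0.9998 |

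**Step 3: size of the selection effect.** If families without access differ by δ in mean outcome from those with access, removing them shifts the mean of Group 3 by p × δ relative to a group that keeps them. The documents do not give δ. With δ assumed to be 0.5 SD, as a yardstick only, the shift is 0.05 × 0.5 = 0.025 SD, 0.10 × 0.5 = 0.05 SD, or 0.251 × 0.5 = 0.13 SD.

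**Step 4: power.** For a two-sided 5% test on post-scores with SD 1 (assumed), 22.5 against 30 families instead of 30 against 30 lowers power from 0.49 to 0.43 at d = 0.5, and from 0.87 to 0.82 at d = 0.8. Even at the highest p, lost power is the smaller issue. The main one is selection.

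**Step 5: keeping these families in the analysis instead.** If families without access gain nothing from an online allocation, the as-allocated effect against usual care is (1 − p) × d. With d = 0.5 this is 0.95 × 0.5 = 0.475, 0.90 × 0.5 = 0.45, or 0.749 × 0.5 = 0.37. The selection is gone, but Group 3 still contains families who could never have received the training.

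**The case against.** **The bias works through another rule.** Lack of access distorts the comparison only because non-watchers and non-completers are dropped. If every randomised family were analysed as allocated, using the measures that Retention already plans to collect, this selection would disappear along with every other kind tied to adherence. This stands, and it is why the access criterion cannot be the whole remedy. It does not remove the point, because Step 5 shows what would remain.

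**Access may be part of effectiveness.** The trial aims at wider reach, so failing to reach an unconnected family could count as part of the effect. That is a defensible target population. The plan does not adopt it, however, because it excludes exactly those families after allocation.

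**A reader might infer that a quarter of the online arm will be lost.** The documents do not support this. The 74.9% is a national household figure, cited to show that online delivery is feasible, with 97% of those users connecting by phone or tablet. The schooling requirement and the exclusion of extreme poverty probably raise access in this sample. A caregiver may also connect outside the home, and the e-mail and WhatsApp reminders suggest a largely connected clientele, although they are not a criterion.

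**A reader might infer that the online arm ends up better off than both other arms.** That is not established either. Modifications also removes face-to-face families who do not attend, and the Discussion lists travel time and expense among the barriers to that format. These too may weigh on poorer families. For the same reason, only internet-caused loss is confined to Group 3, not all inability to use the allocated training.

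**The 30-day allowance and telephone contact** soften loss from intermittent access, but not from having none.

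**The article is condensed.** The full protocol might contain an access criterion. But the article lists eligibility down to schooling and intelligence percentiles and makes those criteria the gate to randomisation.

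**Conclusion.** The point holds in limited form. As written, the plan can randomise a family to a treatment it cannot receive and then exclude it, and for lack of internet this can happen in Group 3 only.

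The number affected is unknown: 1.5 to 3 of 30 if 5% to 10% lack usable access (assumed), and about 7.5 if the national household figure applied, which is an illustration and not a forecast. Against usual care, the loss would probably remove poorer families from the online arm, on the assumption that lack of access is commoner among them. Against face-to-face training, the net direction cannot be determined from the documents. The resulting shift is likely to be modest, but it falls on the online versus face-to-face contrast that is central to a trial described as an equivalence trial. It should be fixed because prevention is cheap.

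**What to change.** Add an inclusion criterion to Eligibility criteria, checked for every family at screening before randomisation: the primary caregiver has regular access to an internet-connected device able to play the modules, and can accept allocation to any of the three groups. The second part also covers families who could not attend the face-to-face sessions. Report in the flow diagram how many families fail the criterion, and describe the trial population accordingly.

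Separately, replace the completer-only rule in Modifications and in Analysis population and missing data with an analysis of all randomised families as allocated, using the measures that Retention collects after dropout. Leaving the training would then no longer mean leaving the analysis. Neither change replaces the other.

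The cost is an amendment and one screening question. With about six new patients screened per week, the effect on recruitment should be small. The real downside is that families without internet will not be represented, which matters for a project aimed at underserved families and should be stated as a limit on generalisability.
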